## Measurements

### Primary outcomes

#### Behavioural outcome

The primary outcome is the decrease of the patient’s BPSD measured as the net change in the NPI-NH total score from baseline to post intervention. We expect a significant difference in NPI-NH total scores between the experimental and active control groups. The NPI-NH has been specifically designed for interviewing professional care facility staff; it has been validated in different countries, and the Italian version of the scale has demonstrated good psychometric properties [22]. It will be administered to the staff by a trained blinded psychologist. The time frame of that evaluation is from baseline (T0) to 30 days after the beginning of the intervention (T2).

#### Professional caregiver distress outcome

A decrease of the professional caregiver distress ratings related to the patient’s BPSD is also expected. It will be measured as the net change in the NPI-NH-D total score from baseline to post intervention [22, 23]. We expect a significant difference in NPI-NH-D total scores between the experimental and active control groups. It will be administered to the staff by a trained blinded psychologist. The time frame of that evaluation is from baseline (T0) to 30 days after the beginning of the intervention (T2).

#### Physiological outcomes

We have planned to monitor three physiological outcomes: blood pressure (systolic and diastolic), heart rate and salivary cortisol level. Blood pressure (systolic and diastolic) and heart rate are biomarkers of acute stress involved in the response to physical and psychosocial stressors. Salivary cortisol level is a biomarker of stress, and its secretion is the final product of the activation of stress-response mechanisms; specifically, the hypothalamic-pituitary-adrenal axis [29]. Changes in its secretion rate were reported during acute responses to stress in the context of illnesses and in cognitive impairment [30], in mood disorders [31] and in individuals with different adult attachment styles [32]. Professional caregivers will collect the saliva samples, blood pressure (systolic and diastolic) and heart rate readings of each participant in both the experimental and control groups, immediately before the treatment and 15 min after the end of treatment at the first and the 30th session of DTI or SI. We expect a significant difference between the experimental and the control group in blood pressure levels and heart rate from the first to the 30th session. A ratio between pre-treatment versus ‘after 15 min’ will be calculated for the first and 30th sessions. We expect a significant difference in the concentration of salivary cortisol between the experimental and control groups from the first to the 30th sessions.

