### Sample size

To our knowledge, at the start of the study on 1 February 2017, no previous study had measured the efficacy of DT using the NPI-NH score. Therefore, a referral upon existing data could not be used in the power calculation. The power analysis was conducted using an estimated medium effect size (*f* = 0.25), an alpha level of 0.05, and a power of 0.8. According to statistical computing, a sample size of *n* = 128 is required, with 64 participants per group, for an analysis of covariance that includes the NPI-NH baseline score as a covariate. We planned an increase in sample size of 13 participants, because the expected drop-out rate is 10% due to possible acute clinical conditions interfering with the participation in the study, or death. In case of a refusal of the object (doll or cube), another participant will be enrolled as a replacement. Participants who underwent less than 60% of sessions will be excluded from analysis. The power calculation was performed with the programme *G*Power* 3.1 [27].

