### Statistical analyses

As a first step, a post hoc evaluation by descriptive statistical comparisons between the intervention and the control groups in age and baseline NPI-NH will be conducted to assess the effectiveness of the randomised assignment. To evaluate associations between biological parameters (decreased, influent, or increased) of each patient at the baseline versus the post intervention, the chi-square test or Fisher’s exact test will be performed. Primary outcomes will be tested performing an analysis of covariance (ANCOVA) of these measurements with the experimental group as the factor baseline NPI-NH and total number and posology of psychopharmacological therapies as the covariates. In order to evaluate how much variance in NPI-NH net change can be explained by groups (experimental versus control groups) after controlling for baseline NPI-NH and biological parameters, a multiple regression analysis will be performed.

Treatment efficacy will be analysed by a per-protocol analysis (PPA) that excludes all drop-outs. Differences will be considered statistically significant when *p* values are lower than 0.05.

All analyses will be conducted using Stata version 13 (Stata Corp., College Station, TX, USA).

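### Cortisol change is defined as a plain before/after ratio that appears to enter ANCOVA; the log ratio is the better scale, and the plan should say which variables and which test the ratio serves

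*Protocol article*

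**What the plan says.** The Physiological outcomes section stands under the Primary outcomes heading of the protocol article. Saliva, blood pressure and heart rate are taken just before and 15 minutes after treatment, at sessions 1 and 30. The only derived quantity defined there is: "A ratio between pre-treatment versus ‘after 15 min’ will be calculated for the first and 30th sessions". No logarithm or other transformation is named.

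The sentence before it concerns levels: "We expect a significant difference between the experimental and the control group in blood pressure levels and heart rate from the first to the 30th". The sentence after it concerns cortisol: "We expect a significant difference in the concentration of salivary cortisol between the experimental and control groups from the first to the 30th sessions". Neither says that the ratio is the quantity compared.

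Statistical analyses then says: "Primary outcomes will be tested performing an analysis of covariance (ANCOVA) of these measurements", with "baseline NPI-NH and total number and posology of psychopharmacological therapies as the covariates". The session 1 value of the physiological measure is not among the covariates. The same section gives the biological parameters a separate categorical analysis, by chi-square or Fisher's exact test: "To evaluate associations between biological parameters (decreased, influent, or increased) of each patient at the baseline versus the post intervention".

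**The concern.** ANCOVA compares arithmetic means. On a plain ratio, a resident whose cortisol halves and one whose cortisol doubles do not average to no change, and the mean ratio rises with the spread of responses even when the typical response is nil. Swapping numerator and denominator changes more than the sign of the answer: it changes the test result. At stake is a primary-listed comparison that may lose power, and whose result hangs on an arbitrary choice of orientation.

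**Working it through.** **The plan's own figure.** Sample size gives "using an estimated medium effect size (*f* = 0.25), an alpha level of 0.05, and a power of 0.8" and concludes that "a sample size of *n* = 128 is required, with 64 participants per group". With f = 0.25 (d = 2f = 0.5), N = 128, two groups and one covariate, the noncentrality is f²N = 0.0625 × 128 = 8 on 1 and 125 degrees of freedom, and power is 0.801. The figure reproduces. It was derived for NPI-NH, so the choice of physiological scale does not alter it.

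**Asymmetry.** Take one halving and one doubling of cortisol.
- Pre/after: (2 + 0.5)/2 = 1.25, which reads as a fall.
- After/pre: (0.5 + 2)/2 = 1.25, which reads as a rise.
- Log scale: (ln 2 − ln 2)/2 = 0, a geometric mean ratio of 1.

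A 1.5-fold pair averages 1.083 and a 1.25-fold pair 1.025, so the problem shrinks quickly for small changes.

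**Dependence on spread.** If the log ratio is normal with mean 0 and SD s, the mean ratio is exp(s²/2): 1.005 at s = 0.1, 1.083 at 0.4, 1.197 at 0.6 and 1.377 at 0.8.

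**Power.** The protocol gives no SD for any physiological measure, so every log-SD here is an assumption. The simulation used 64 per arm, log-normal ratios, correlation 0.3 between sessions, the same spread in both arms and 20,000 replicates. The tested quantity was the change from session 1 to session 30, with the true effect set to give 80% power on the log scale. That effect is about 0.5 × s × √(2 × 0.7): 0.47 at s = 0.8, about a 1.6-fold difference, and 0.59 at s = 1.0, about 1.8-fold.

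| Assumed log-SD | Log ratio | Plain ratio, effect raises it | Plain ratio inverted |
|---|---|---|---|
| 0.8 | 80% | about 72% | about 53% |
| 1.0 | 80% | about 64% | about 43% |

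Repeat runs differ by about one percentage point.

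**False positives.** Same design, no true median change, two-sided 5% level, plain ratio:

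| Assumed log-SDs at session 30 | Change, equal spread at session 1 | Session 30 alone | Change, same spread difference at both sessions |
|---|---|---|---|
| 0.4 v 0.6 | 13.9% | 14.6% | 5.1% |
| 0.4 v 0.7 | 24.7% | 24.8% | 4.8% |
| 0.5 v 0.8 | 23.6% | 23.7% | 4.8% |

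The log ratio stays at about 5% throughout. In a separate run with uncorrelated sessions and ANCOVA on one covariate, equal spreads gave 4.9% and 5.0% (log-SD 0.3 and 0.5 in both arms, session 30 alone). A milder divergence of 0.3 v 0.4 gave 7.4% for session 30 alone and 6.5% for the change. At small spreads, assumed to resemble blood pressure and heart rate, session 30 alone gave 5.6% (0.05 v 0.10) and 5.9% (0.10 v 0.15).

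**The case against.** The strongest reply is that the plan never states the sequence being criticised. The ratio is not named as the ANCOVA outcome, it is not tied to cortisol, and the neighbouring sentences speak of levels and concentration. The ratio might serve only to sort residents into the categories of the chi-square analysis, and categories set symmetrically on a fold scale would escape the asymmetry. A logarithm might also be specified in an analysis plan that is not shown. This stands as a limit: entry into ANCOVA is an inference. It is a direct one, because the ratio is the only derived physiological measure defined and ANCOVA is the stated test for primary outcomes. The categorical analysis is not said to replace that test.

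A reader might go further and infer that the plan will produce a false cortisol effect, because the Secondary goal section expects acceptance, rejection and inconsistent reactions to the doll. The documents do not support that. That section predicts behaviour by attachment style among residents given the doll; it does not predict greater cortisol variance than with the cube. Session 1 already uses the doll or cube, and the Discussion concedes that no stress level free of the intervention is collected. A doll-related difference in spread could therefore be present at both sessions, and the change in ratio then keeps its 5% level. The covariate list does not settle whether the change or session 30 alone is compared, so the risk is neither established nor excluded.

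**Conclusion.** The point holds as a modest specification fault, worth correcting, and chiefly for cortisol. The plan states a plain ratio for outcomes listed as primary. Read with the ANCOVA sentence, that is a scale on which equal fold rises and falls do not cancel and the orientation affects the result.

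The firmest consequence is lost power when spread is large, and it needs no difference in spread between arms: from 80% to about 72% or 64%, or to about 53% or 43% inverted, at assumed log-SDs of 0.8 or 1.0. False-positive rates of about 14–25% are conditional. For the spread pairs assumed, they arise only if the arms differ in spread at session 30 and either session 30 alone is compared or the spreads were equal at session 1. Blood pressure and heart rate are barely affected if their spread is as small as assumed. The sample size of 128 is unaffected.

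**What to change.** In Physiological outcomes, replace the ratio sentence for cortisol with log(after 15 min) minus log(pre-treatment) at each session. Name this as the ANCOVA outcome, say whether the session 30 value or the change from session 1 is compared, and report a geometric mean ratio with 95% CI. State that blood pressure and heart rate use plain differences.

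This needs no new data, visits or participants. The small cost is that cortisol results are reported as percentage change. On the log scale, reversing the ratio only changes the sign.

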#### Interaction with the object outcome

We expect an increase of the interaction with the object (doll or cube), as exploration and caregiving behaviours during the object presentation. These measures will be recorded at the first and the 30th sessions by a trained psychologist who will fill an observational grid. It is a non-validated instrument developed for the aims of the present study that includes four areas related to different kinds of behavioural responses in a dichotomous way (behaviour: present/absent; see Table 1): object presentation, separation from the nurse, behaviours during the interaction with the object and separation from the object. We expect a significant difference in frequency of the interactions with the object from the first to the 30th session between the experimental and control groups.

### Secondary outcomes

#### Confirmation of stability of attachment style

Assessment of premorbid attachment style of PWD (Adult Attachment Interview (AAI)).

We have planned to study 30 patient-offspring couples (about 47% of the participants in the experimental group). When offspring who regularly visit the patient have accepted the interview, the AAI will be administered to a son or daughter of a patient among those in the DTI group. The AAI is a semi-structured interview designed to evaluate attachment styles in adult populations and allows us to identify three different categories of mental states related to the attachment style of the son or daughter of the PWD: free, dismissing/preoccupied, or unresolved. Free adults have positive internal representations about past relationships with their parents and feel free to explore their infant experience. Dismissing or preoccupied adults (categorised as insecure attachment) fail in telling coherent attachment stories about their parents; they are inclined to idealise or denigrate the role of their parents in the past. Unresolved adults show problems with past mourning experiences and unresolved trauma occurring during infancy. Since a correspondence of 75% between the individual’s attachment and that of their children has been reported [33], we can hypothesise that the AAI is a useful instrument to infer the premorbid attachment style of PWD. This semi-structured interview will be administered in the nursing home and will be video-recorded. The coding of the answers will be carried out by an external trained and authorised psychologist.

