### Secondary goal

The secondary goal is the confirmation of the hypothesised stability of the past attachment style of the PWD (provided by the Adult Attachment Interview (AAI) [24] administered to the patients’ offspring (family caregivers), even in the advanced stages of dementia. The current attachment style of the PWD is provided by the observations of the patient during a situation of meeting-separation from their own family caregiver. These evaluations will be conducted, after conclusion of interventions, among a sub-group of participants in the experimental condition. We expect to find an association between the past and the current attachment style of the PWD, categorised as secure, insecure, and unresolved. Furthermore, the relationship between patients’ attachment styles and the response to DTI in terms of caregiving behaviours towards the doll (e.g. caressing the object, talking to it and smiling) will be investigated. We expect that PWD with a previous secure attachment style will accept the doll and will show more caregiving behaviours compared to PWD with insecure attachment style, while these latter will show more rejection, avoidance or excessive caregiving reactions towards the doll. We also expect that PWD with unresolved attachment style will show inconsistent responses to the doll presentation, with approaching and rejecting behaviours.

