#### Assessment of current attachment style of the PWD

After the interview, family caregivers will be invited to visit their relative. They will meet in a room of the nursing home and the task will be based to some extent upon ‘Ainsworth’s strange situation’, an experimental research setting originally conceived to observe young children. This situation will aim to facilitate exploration of possible attachment behaviours under different conditions. The visit will last about 15 min. There will be four distinctive stages:
The patient is together with the researcher, a trained psychologist in the role of stranger in a room. The family caregiver meets the patient. It is an unexpected visitThe family caregiver indicates, by talking and/or gesturing, that they must leave and suddenly ends the visit. This creates a potentially threatening moment for the PWDThe patient is once again in the room with the strangerThe family caregiver comes back to the room

The whole visit will be video-recorded. The occurrence of attachment behaviours will be determined afterwards by interval sampling. The presence or absence of attachment behaviours will be registered on an observational grid, a non-validated instrument developed for the present study (see Table 2).

We expect the stability of the attachment style of the PWD in term of a correlation between the premorbid attachment style and the current one. We also expect a correlation between the patients’ attachment styles and their response to DTI.

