The attachment styles are recognised as being persistent during the ageing phases as demonstrated by previous studies based on the AAI, but the PWD cannot be interviewed. To date, there are no studies which have overcome this limitation. Moreover, the attachment style, experienced with the attachment figure since birth, may change during the life cycle. The experiences with other significant and the new adaptations to the demands posed by the various stages of life exert their influence acting as corrective. It is possible that, in the advanced stages of dementia, these adaptations could be lost due to the deterioration of capability of access to the meaning of emotional states. The comprehension of the attachment style of the PWD is of key importance, so that caregivers can interpret and respond to specific modalities of the PWD to ask for closeness and protection [37].

A limitation of this study is the exclusion of men. This is because women are 71.6% of patients with dementia living in nursing homes of the Canton Ticino, as reported by the Department of Health and Sociality of the Canton Ticino (source: Statistica intra-muros, SOMED, Dipartimento della sanità e della socialità, Unità statistiche sanitarie, Bellinzona). The authors have chosen to exclude men in order to have the most homogeneous sample in the time frame of the study, but further research is needed in order to demonstrate the feasibility of DT in men. The need for attachment and the ability to provide assistance are linked to the innate drive to give security and comfort to an individual who presents physiognomic characteristics of fragility and vulnerability (small nose, high forehead, soft skin). These characteristics activate caregiving behaviours and oxytocin increase, supporting the caregiving activity: this is not about gender but about characteristics belonging to all humankind [38]. Physiological parameters will always be monitored during the interventions (first or 30th session) both for the experimental (doll) and active control groups (cube), but we will not collect the basal stress levels prior to any interference of the intervention (cube or doll).

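### The offspring's own AAI category stands in for the patient's past style, and the same offspring is the partner in the test of her current style, so a correlation between the two cannot confirm stability

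*Protocol article*

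**What the plan says.** The Secondary goal section states the aim: "The secondary goal is the confirmation of the hypothesised stability of the past attachment style of the PWD". The section Confirmation of stability of attachment style repeats it in its title.

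The *past* style is obtained as follows: "the AAI will be administered to a son or daughter of a patient among those in the DTI group". The interview yields "three different categories of mental states related to the attachment style of the son or daughter of the PWD", so what is classified is the offspring. The step from offspring to patient is one cited figure, "Since a correspondence of 75% between the individual’s attachment and that of their children has been reported", from which the text concludes that "we can hypothesise that the AAI is a useful instrument to infer the premorbid attachment style of PWD". The trial does not test that step.

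The *current* style comes from an observed visit with four stages: meeting, departure, absence and return of the family caregiver. The interviewed person and the visitor are the same. The Secondary goal section describes the AAI as "administered to the patients’ offspring (family caregivers), even in the advanced stages of dementia", and the section on current attachment style says "After the interview, family caregivers will be invited to visit their relative". The grid in Table 2 mainly scores the patient's responses to her child.

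Both measures are taken after the interventions end, in 30 pairs from the doll arm. The section on current attachment style takes a correlation between the two as the expected sign of stability.

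**The concern.** A stability claim needs information on the patient at two times. Here there is one observation of the patient and one interview of someone else. A proxy for the past can support the claim only if the offspring's category is related to the patient's present behaviour solely through her own past style. Observing her with that same offspring removes this condition. How a mother responds to her child today may depend on that child's own attachment category, whatever her style was before the illness.

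At stake is an unsupported published conclusion: concordance in today's mother-child pair reported as persistence of the mother's style through advanced dementia. The same proxy also enters the planned analysis of *past* style against caregiving behaviour towards the doll.

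**Working it through.** **The plan's own figure.** 30 / 64 = 46.9%, which matches the stated share of about 47% of the doll arm.

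**Inputs from the article.** Three categories, 75% parent-child correspondence, 30 pairs.

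**Assumptions, not in the article.**
- Category prevalences are one third each, or 55/30/15%.
- The 75% is read as a match across the three categories.
- The grid codes without error.
- With probability d, the patient's current category follows the offspring's category (within-pair effect). Otherwise it equals her past category with probability s (stability), or is a fresh draw from the prevalences.

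**Formulas.** Chance agreement e is the sum of squared prevalences. Chance-corrected transmission is a = (0.75 − e)/(1 − e).
- Equal prevalences: e = 1/3, a = 0.4167/0.6667 = 0.625.
- 55/30/15: e = 0.3025 + 0.09 + 0.0225 = 0.415, a = 0.335/0.585 = 0.573.

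Expected agreement between AAI and current category is d + (1 − d)[e + s·a·(1 − e)]. Subtracting e and dividing by 1 − e gives

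kappa = d + (1 − d)·s·a.

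The data supply one association, and it depends on both s and d. With equal prevalences, kappa = 0.625 arises from:
- s = 1, d = 0: 0.625
- s = 0.5, d = 0.4545: 0.4545 + 0.5455 × 0.3125 = 0.625
- s = 0, d = 0.625: 0.625

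**Simulated chi-square test** (30 pairs, alpha 0.05, 10,000 replicates). Each cell shows equal prevalences / 55-30-15.

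| Case | AAI-current agreement | kappa | Significant | Patient's true past-current agreement |
|---|---|---|---|---|
| Full stability, no pair effect | 75% / 75% | 0.625 / 0.573 | 98.2% / 94.3% | 100% / 100% |
| No stability, d = a, 75% correspondence | 75% / 75% | 0.625 / 0.573 | 98.3% / 94.0% | 59.4% / 60.7% |
| No stability, d = a, no correspondence | 75% / 75% | 0.625 / 0.573 | 98.3% / 94.1% | 33.3% / 41.5% (chance) |
| No stability, d = 0.4, 75% correspondence | 60% / 64.9% | 0.400 / 0.400 | 66.1% / 66.9% | 50.0% / 54.9% |
| Half stability, no pair effect | 54.2% / 58.3% | 0.312 / 0.286 | 43.8% / 40.2% | 66.7% / 70.8% |
| No stability, no pair effect | 33.3% / 41.5% | 0 / 0 | 4.8% / 4.9% | 33.3% / 41.5% |

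The first three rows look alike to the planned analysis. In the second row the patient's past and present agree above chance only because both resemble the offspring. The third row drops the correspondence altogether, so the AAI carries no information on her past, and the test is still almost always significant.

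**Attenuation.** With d = 0, kappa = s·a, so the proxy scales the association by 0.625 or 0.573. At 75% correspondence, 0.25 × 30 = 7.5 of the 30 inferred past styles are expected to be wrong.

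**The case against.** The best defence is that patients in advanced dementia cannot be interviewed, as the Discussion says, so some proxy is unavoidable. The text hedges the proxy as a hypothesis. The AAI deals with the offspring's account of past relationships with parents, so its content is retrospective although it is taken now. Table 2 also has an item on turning toward the stranger. The Discussion concedes that "the attachment style, experienced with the attachment figure since birth, may change during the life cycle". All of this stands, but none of it separates the offspring's influence on the visit from the patient's own past style. The stated limitations (exclusion of men, no basal stress levels, no cost-effectiveness evaluation) do not mention it.

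Three stronger readings are tempting, and the article does not support them.

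- *That imperfect correspondence would be reported as instability, so no result could be informative.* The plan tests an association. It never compares agreement with 100% or counts discordant pairs as changed patients. Under perfect stability and error-free coding, the test would miss in only about 2% to 6% of studies, so a null result would count against strong stability.
- *That a true proportion stable can be worked back from the observed agreement.* If c is the agreement with the AAI category among changed patients, then 0.50 = 0.75s + c(1 − s) gives s = 67%, 60% or 50% for c = 0, 0.125 or 0.25. The article does not fix c, and the calculation assumes no within-pair effect, which is the very thing that cannot be excluded.
- *That the interview itself distorts the visit.* The article says only that the visit follows the interview and gives no interval. Any carry-over is conjecture, and the shared-offspring problem does not need it.

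**Conclusion.** The point holds as a construct-validity fault in a secondary aim. As written, a positive correlation would be taken as confirming stability of the patient's style, although the two measures share the same offspring and the design cannot separate stability from concordance within the pair. The 75% correspondence, if it holds, further weakens the association even under perfect stability.

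That the two explanations cannot be separated follows from the measurement design. The percentages rest on the assumed prevalences, the error-free grid and the assumed within-pair effect. The article gives no strength for that effect, and the calculation does not show that it exists. A smaller effect would mimic stability less often: about 66% to 67% significant at d = 0.4.

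The randomised primary comparison and its sample size of 128 are not touched.

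**What to change.** 1. In Secondary goal, Confirmation of stability of attachment style (title included) and Assessment of current attachment style of the PWD, restate the aim and its permitted conclusion as exploratory concordance between the offspring's AAI category and the patient's current behaviour towards that offspring. Remove the wording that promises confirmation of stability.
2. In the limitations within the Discussion, state that the past style is a proxy taken from the offspring, that the same offspring is the partner in the observed visit, and that together these prevent a conclusion on stability.
3. Carry the proxy limitation over to the analysis of *past* style against response to the doll. The explanatory variable there is the offspring's category, not a measured style of the patient.

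The cost is wording only, with a more modest secondary claim. No data collection changes. Two additions are better left out. An implied-stability estimate would assume away the within-pair effect. Reversing interview and visit near the expected finish in February 2020 would mix two procedures within 30 pairs and leave the shared offspring in place.
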